## Abstract

**Background:**

Patients diagnosed with pancreatic, biliary tract, and liver cancer often suffer from a progressive loss of muscle mass. Given the considerable functional impairments in these patients, high musculoskeletal weight loads may not be well tolerated by all individuals. The use of blood-flow restricted resistance training (BFR-T) which only requires low training loads may allow for a faster recovery of muscle due to avoidance of high levels of mechanical muscle stress associated with high-load resistance exercise. This study aims to investigate whether BFR-T can prevent or slow down the loss of skeletal muscle mass and enhance the functional capacity and mental health of patients with pancreatic, biliary tract, and liver cancer.

**Methods:**

The PREV-Ex exercise trial is a multicenter two-armed randomized controlled trial. Patients will be randomized to an exercise program consisting of home-based low-load BFR-T during a combined pre- and postoperative period for a total of 6–10 weeks (prehabilitation and rehabilitation), or to a control group. Protein supplementation will be given to both groups to ensure adequate protein intake. The primary outcomes, skeletal muscle thickness and muscle cross-sectional area, will be assessed by ultrasound. Secondary outcomes include the following: (i) muscle catabolism-related and inflammatory bio-markers (molecular characteristics will be assessed from a vastus lateralis biopsy and blood samples will be obtained from a sub-sample of patients); (ii) patient-reported outcome measures (self-reported fatigue, health-related quality of life, and nutritional status will be assessed through validated questionnaires); (iii) physical fitness/performance/activity (validated tests will be used to evaluate physical function, cardiorespiratory fitness and maximal isometric muscle strength. Physical activity and sedentary behavior (assessed using an activity monitor); (iv) clinical outcomes: hospitalization rates and blood status will be recorded from the patients’ medical records; (v) explorative outcomes of patients’ experience of the exercise program which will be evaluated using focus group/individual interviews.

**Discussion:**

It is worthwhile to investigate new strategies that have the potential to counteract the deterioration of skeletal muscle mass, muscle function, strength, and physical function, all of which have debilitating consequences for patients with pancreatic, biliary tract, and liver cancer. The expected findings could improve prognosis, help patients stay independent for longer, and possibly reduce treatment-related costs.

**Trial registration:**

ClinicalTrials.gov NCT05044065. Registered on September 14, 2021.

## Administrative information

Note: the numbers in curly brackets in this protocol refer to SPIRIT checklist item numbers. The order of the items has been modified to group similar items (see http://www.equator-network.org/reporting-guidelines/spirit-2013-statement-defining-standard-protocol-items-for-clinical-trials/).

## Introduction

### Background and rationale {6a}

Patients with resectable pancreatic, biliary tract, or liver cancer are at increased risk of skeletal muscle loss attributed to several factors including surgery, disease burden, inactivity, and treatment [1, 2]. Skeletal muscle wasting occurs as early as 1 to 2 years before pancreatic cancer diagnosis and can lead to cachexia, a debilitating and ubiquitous condition characterized by an ongoing accelerated loss of skeletal muscle mass leading to progressive functional impairments [1, 3]. No drug or nutritional interventions have to date been proven effective against cachexia [4]. Given the complexity of cancer cachexia, its successful management will require an intervention with pleiotropic effects. Resistance exercise produces multifactorial and anabolic stimuli [5] and acts on several signaling pathways to antagonize muscle atrophy in cachexia. In cachectic mice, resistance training by ladder climbing counteracted muscle wasting and improved survival [6]. Moreover, some of the few randomized exercise trials in patients with pancreatic cancer showed that supervised resistance training was safe, feasible, and improved muscle strength [7] and quality of life [8]. Despite advanced disease, patients with pancreatic cancer are willing and interested in participating in an exercise intervention [9]. However, given the considerable functional impairments and muscle loss faced, high-load exercise may not be well tolerated by all individuals. One resistance training modality, namely blood flow restriction training (BFR-T), that incorporates low‐load resistance training with concurrent partial restriction of blood flow to the working muscles, induces substantial gains in muscle strength and muscle mass in both frail elderly [10] and in patients with myopathy [11]. Despite the beneficial effects on skeletal muscle, only one study explored BFR-T in patients with cancer demonstrating its feasibility and effectiveness in enhancing physical function with 4 weeks of pre-surgery intervention in patients with abdominal cancer [12]. Due to the low muscle loading, BFR-T could serve as a feasible exercise modality in patients with cancer that can be implemented safely both at home and in the clinic. Given the heightened risk of infection and reduced ability to travel during active treatment, a safe and effective home-based exercise intervention is preferred by patients. Furthermore, perioperative interventions like BFR-T could potentially minimize adverse events (AEs) and improve surgery-related outcomes. Minimal equipment, low-weight loads, or body weight loads are required to carry out BFR-T, making the future implementation of such a training strategy highly attractive.

### Objectives {7}

The *overall objective* of this randomized controlled trial is to examine if low load BFR-T can prevent muscle atrophy or mitigate its progression by studying changes in muscle mass and muscle signaling in patients with resectable pancreatic, biliary tract, or liver cancer.

Using a two-armed randomized controlled trial *the primary aim* of this project is to assess if a BFR-T program can preserve or increase skeletal muscle mass measured as thickness and cross-sectional area in patients with resectable pancreatic, biliary tract, or liver cancer.

The *secondary aims* are to investigate the effects of BRF-T on:Myogenic stem cells, mitochondrial function, capillarization, macrophage infiltration, and muscle catabolism, measured in skeletal muscle biopsies from a subgroup of voluntary participantsMuscle strength, physical function, body composition, and physical activity levelsSelf-reported fatigue, health-related quality of life (HRQoL), and nutritional statusThe patients’ experience of the exercise programHospitalization, prognostic markers, and different blood status concentrations

The use of BFR-T using low training loads may allow for a quick postoperative recovery by avoiding the high levels of mechanical muscle stress typically associated with high-load resistance exercise. Thus, BFR-T could serve as a feasible exercise modality in this patient population to mitigate the burden of cachexia. Moreover, the metabolic stress induced by BFR-T may have the potential to normalize the disrupted intramuscular milieu in cachectic muscle leading to a proper muscle regenerative response. Therefore, it is expected that the challenge imposed by BFR-T will:Stimulate muscle hypertrophy and thereby preserve or increase muscle massInduce beneficial effects on skeletal muscle characteristics in terms of myogenic stem cell count and differentiation, basal autophagy activity, mitophagy/biogenesis, capillaries per muscle fiber, macrophage infiltration, and reduce the levels of catabolic markersImprove muscle strength, physical function, and physical activity levelsCounteract an increase in self-reported fatigue and a decline in HRQoLDue to its proposed positive effects on skeletal muscle mass and quality, lead to lower hospitalization rates

### Trial design {8}

This Prev-Ex is a multi-center, two-armed randomized controlled trial (RCT) with 1:1 allocation ratio, stratified for research site, and testing the superiority of the intervention. Patients diagnosed with resectable pancreatic, biliary tract, and liver cancer are randomized to an exercise program consisting of home-based low-load BFR-T during both a pre- and postoperative period consisting of a total of 6–10 weeks, or a control group. Besides the nutritional support offered as standard care for these patients, protein supplementation will be given to both groups to ensure adequate protein intake. See Fig. 1 for the modified SPIRIT study flow chart.

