### Participant timeline {13}

Study outcomes will be measured at baseline (T0) and immediately (1–4 weeks) after the prehabilitation period (T1), after surgery prior to the rehabilitation period (T2), and after the 5–6-week postoperative rehabilitation period (T3). A follow-up assessment (T4) will take place 6 months following surgery. Patients with short time-to-surgery will only perform (T0) prior to surgery or will be included at (T2) for the rehabilitation period. Focus group or individual interviews will take place sometime following the exercise intervention. Hospitalization rates, prognostic- and blood markers will be assessed retrospectively at (T4) through the patients’ medical records. Baseline testing will begin immediately as participants are recruited and randomization will occur directly after the initial testing session (T0). Exercise training for the intervention group will start once participants have completed baseline testing. See Fig. 2 for an overview of the study design and measurement outcomes and time points.

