## Statistical methods

### Statistical methods for primary and secondary outcomes {20a}

Data will be analyzed using the IBM SPSS (Statistical Package for the Social Sciences) 26 statistical package for Windows (SPSS, Chicago, IL, USA). For the quantitative analysis, descriptive statistics, ANOVA, and chi-squared tests will be used to describe and compare baseline characteristics. For longitudinal analysis, linear mixed modeling adjusted for baseline values (T0) of the outcome will be used to detect any significant differences between the two groups from pre- to post-intervention as well as at follow-up 6 months following surgery. Group-by-time interaction will be included as a fixed effect. Corresponding effect sizes will also be calculated. Chi-squared tests and corresponding odds ratios will be calculated for hospitalization rates. All tests will be 2-tailed and statistical significance set at *p* ≤ 0.05.

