### Methods for additional analyses (e.g., subgroup analyses) {20b}

For the primary outcome the model will, besides being adjusted for the baseline value, also be adjusted for diagnosis and type of surgery. Per protocol analysis for those who have adhered to the exercise program will be performed. Potential moderators of the exercise effect will be explored (e.g., age, sex, type of surgery, diagnosis). In addition, mediation analyses will be performed to explore potential underlying mechanisms of exercise effects (e.g., blood and muscle biomarkers). A subgroup analysis will also be performed to assess the rehabilitation effect only considering that some patients have a very limited time to exercise prior to surgery or may not be included until T2 due to very short time-to-surgery.

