Due to the COVID-19 pandemic, the study start was delayed for almost 1 year. The initial plan was to include a more homogenous group: patients diagnosed with pancreatic or biliary tract cancer undergoing a pancreaticoduodenectomy; however, there were major challenges with the inclusion rate resulting in the study taking longer and risking a loss of statistical power. Amendments were made to the original plan to expand the inclusion criteria to patients undergoing either pancreaticoduodenectomy or laparoscopic surgery and to also patients with malignancies in the liver amendable for surgical resection. These changes were approved by the Swedish Ethical Review Authority and the Norwegian Regional committees for medical and health research ethics. We are aware that this will result in a heterogeneous group of patients. There is considerably less risk of complications for patients undergoing laparoscopic surgery compared to a pancreaticoduodenectomy; however, these potential differences will be adjusted for in the statistical analysis. Moreover, time to surgery and post-surgery recovery are similar across the diagnoses. In this study, we decided to include any patient who is diagnosed with resectable pancreatic, biliary tract, or liver cancer regardless of time-to-surgery which means that some patients will only have time to perform (T0) before surgery, while some will perform both (T0) and (T1). In some cases, time-to-surgery is only a few days which means that inclusion is not possible at (T0) but will instead take place at (T2). The reason for including patients at (T2) is that time-to-surgery is significantly shorter at the Norwegian site; consequently, amendments to the original plan had to be made to accommodate for the reduced time-to-surgery. We will perform a subgroup analysis to evaluate the rehabilitation effect (T2 to T3). Other amendments to the original plan include the addition of digitally supervised exercise and an exercise diary to be able to monitor exercise adherence more efficiently.

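### The primary model adjusts for a T0 value that patients first included at T2 cannot have, so the claim of intention-to-treat analysis without imputation fails for them

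*Protocol article*

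**What the plan says.** All references are to the protocol article.

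**Programme.** Trial design {8} sets the comparison as "home-based low-load BFR-T during both a pre- and postoperative period consisting of a total of 6–10 weeks, or a control group". The Abstract (Methods) likewise describes training before and after surgery: "home-based low-load BFR-T during a combined pre- and postoperative period for a total of 6–10 weeks (prehabilitation and rehabilitation". Intervention description {11a} gives the parts: 1–4 weeks before surgery and 5–6 weeks after it.

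**Entry.** Participant timeline {13} says: "Patients with short time-to-surgery will only perform (T0) prior to surgery or will be included at (T2) for the rehabilitation period". The Discussion gives the reason: for some patients "time-to-surgery is only a few days which means that inclusion is not possible at (T0) but will instead take place at (T2". It links this to shorter time-to-surgery at the Norwegian site. It also says of those who enter at T0 that "some patients will only have time to perform (T0) before surgery, while some will perform both (T0) and (T1".

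**Randomisation.** Participant timeline {13} states that "randomization will occur directly after the initial testing session (T0". Sequence generation {16a} is more general and says only that allocation follows the baseline assessments.

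**Analysis.** Section {20a} specifies "linear mixed modeling adjusted for baseline values (T0) of the outcome will be used to detect any significant differences between the two groups". Section {20b} says the primary-outcome model will, "besides being adjusted for the baseline value, also be adjusted for diagnosis and type of surgery". Section {20c} lists T1 to T4 as the data in the mixed model and concludes that intention-to-treat analysis is possible without imputation. Sections {20b} and the Discussion add a subgroup analysis of the rehabilitation effect, T2 to T3.

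**The concern.** The rules for randomisation and baseline are written for someone who attends T0. A patient first included at T2 never attends it.

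A linear mixed model tolerates missing outcome values, but that tolerance does not extend to covariates. A patient with no value for a covariate contributes no usable record to a standard fit. The reason section {20c} gives for doing without imputation therefore does not cover T2 entrants. The same section counts T2 as outcome data, although T2 is the only measurement these patients have before randomisation.

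At stake is whether some randomised patients leave the primary analysis because of a covariate rule. If they are kept, the question is which baseline is used for them. Keeping them also affects what the overall result describes, because they receive only the postoperative part of the programme.

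**Working it through.** **1. Rules set against the T2 route**

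| Rule | Patient entering at T0 | Patient entering at T2 |
|---|---|---|
| Randomised directly after T0 testing ({13}) | Applies | Cannot apply |
| Model adjusted for the T0 value ({20a}) | Value exists | No value exists |
| T2 counted as outcome data ({20c}) | Post-randomisation visit | Only pre-randomisation visit |
| Training before and after surgery ({8}) | Planned, though time may be short | After surgery only |

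The T2-to-T3 subgroup analysis gives a separate rehabilitation estimate. It does not say whether T2 entrants are in the primary model, or with which baseline.

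**2. Programme received**

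- Planned total: 1 + 5 = 6 weeks to 4 + 6 = 10 weeks, as declared.
- T2 entry: 5 to 6 weeks. Six weeks meets the declared minimum, but none of it is before surgery.
- Sessions ({11a}): before surgery 1 × 4 = 4 to 4 × 5 = 20; after surgery 5 × 2 = 10 to 6 × 3 = 18. The full programme has 14 to 38 sessions and T2 entry has 10 to 18.

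**3. The plan's own sample size**

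Inputs from Sample size {14}: difference 1 mm, standard error of measurement 0.8 mm, two-sided alpha 0.05, power 80%, total 42. Assume that the SD of change is 0.8 × √2 = 1.131 mm. The normal-approximation formula for two means then gives 21 per arm, or 42 in total, which matches. With 21 per arm and a two-sample t-test, exactly 80% power implies an SD of 1.13 mm. That SD is used below.

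**4. T2 entrants dropped**

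The article gives no T2 share, so f = 10%, 25% and 50% are assumptions. Evaluable N = 42(1 − f), and the standard error rises by 1/√(1 − f).

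| f | N left | SE ratio | Power for 1 mm |
|---|---|---|---|
| 0 | 42 | 1.000 | 80% |
| 10% | 37.8 | 1.054 | 75% |
| 25% | 31.5 | 1.155 | 67% |
| 50% | 21 | 1.414 | 49% |

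**5. T2 entrants kept**

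N stays at 42, with one degree of freedom spent on entry pathway. If T2 entrants have the full 1 mm effect, power is about 80%. If they have half of it (an assumption), the average effect is (1 − f) × 1 + f × 0.5 mm.

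| f | Average effect | Power, half effect | Power if dropped |
|---|---|---|---|
| 10% | 0.95 mm | 76% | 75% |
| 25% | 0.875 mm | 69% | 67% |
| 50% | 0.75 mm | 56% | 49% |

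Under the half-effect assumption, keeping these patients gains between 1 and 7 percentage points of power.

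**The case against.** The best defence is that the T0 label is left over from before the T2 route was added. The Discussion says the trial was amended to take in patients with short time-to-surgery, and that slow inclusion threatened power. Recruiting these patients and then deleting them would defeat that purpose. The general wording in {16a} and {20b} fits T2 as an entry baseline. The route is disclosed, a T2-to-T3 analysis is planned, and baseline definitions are often left to an analysis plan that is not shown here.

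Much of this stands. Deletion is probably not intended, and the route is not hidden. But the article does not leave baseline open: {20a} writes T0, {13} ties randomisation to T0, and {20c} draws the intention-to-treat conclusion. An analysis plan that kept T2 entrants would have to depart from the published text.

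A reader might infer four stronger things, which the documents do not support:

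- **Bias between the arms.** If T2 entrants are randomised after T2 testing and kept, the comparison remains a valid randomised one. It also fits the stated aim, which names no timing.
- **A known loss of power.** The article says only that T2 inclusion happens in some cases. A 50% share would be extreme for a route tied mainly to one of two sites.
- **A misleading description of the programme.** The Discussion discloses that some patients miss the preoperative part. Aligning the Abstract and {8} is a matter of wording.
- **A fixed dilution of the effect.** A T2 contrast that shrinks with the T2 share would require the entry measurement of T2 entrants to be counted as their outcome, which is an unlikely coding. It would say nothing about T3.

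**Conclusion.** The point holds as a contradiction in the published rules. The model in {20a} needs a T0 value, T2 entrants cannot have one, and the no-imputation claim in {20c} is therefore wrong for them as written. The subgroup analysis does not repair this. The correction should be made before the data are analysed.

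Its size is uncertain. Power of about 75%, 67% or 49% after dropping T2 entrants depends on assumed shares of 10%, 25% and 50%, and on T2 entrants being lost from the 42 in proportion to their share. Nor should the repair be credited with restoring 80% power, since that requires T2 entrants to have the full 1 mm effect from postoperative training alone. The firm gain is that all randomised patients with follow-up data stay in the primary analysis under a stated baseline.

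**What to change.** 1. **Randomisation and baseline.** In {13} and {20a}, define both by the entry visit: T0 for T0 entrants, T2 for T2 entrants.
2. **Outcome visits.** In {20c}, do not count T2 as an outcome for T2 entrants.
3. **Covariate.** Add entry pathway to the primary model, and let the baseline slope differ by pathway if needed, because one baseline is taken before surgery and the other after it.
4. **Description.** In the Abstract and {8}, state the two entry routes, and that T2 entrants receive only the 5–6 postoperative weeks. Describe the overall result as the effect of offering BFR-T regardless of time-to-surgery.

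**Cost.** No new measurements are needed, because the entry visit and the T2 value are already collected. Coding of baseline and visits becomes slightly more complex. The added covariate overlaps with site, since short time-to-surgery is mainly a feature of one site. Pre- and postoperative baselines are pooled in one model.

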**Fig. 1 Fig1:**
[figure not shown]
Schedule of enrolment, interventions, and assessments in the PREV-Ex trial*. T0 diagnosis or post neoadjuvant chemotherapy; T0–T1 Prehabilitation period 1–4 weeks; *Surgery to discharge from hospital (2–3 weeks); T2–T3 post-surgery training period 5–6 weeks; T3–T4 follow-up 6 months following surgery

## Methods: participants, interventions, and outcomes

### Study setting {9}

Patients will be recruited from two sites: Karolinska University Hospital in Stockholm, Sweden, and Oslo University Hospital in Oslo, Norway. Testing of the participants’ physical fitness and body composition will take place in Stockholm at the research gym laboratory (Rörelseglädjelabbet), Karolinska University Hospital, and in Oslo at the exercise testing facilities at the Norwegian School of Sport Sciences.

### Eligibility criteria {10}

Inclusion criteria are as follows: 18 years or older, males or females, diagnosis of resectable pancreatic cancer, biliary tract cancer, or malignancies in the liver amendable for surgical resection, can maintain oral food intake during the intervention period, ECOG status < 2. Exclusion criteria include ongoing infection, serious neurological or cardiac disease, uncontrolled pain, pregnancy, difficulties breathing, and other contraindications to exercise.

### Who will take informed consent? {26a}

At both sites, a member of the medical staff will screen a potential patient before their hospital visit following the multidisciplinary meeting if eligible. At the hospital visit, the patient is provided with study information in written form, and is asked if a project manager from the research labs may contact the patient by phone. At the Swedish site, patients will, after a reasonable time for reflection, be contacted by a telephone call and will be asked if they are willing to participate. At the Norwegian site, patients will initially be informed about the study through a text message by the research team asking patients to answer whether they are willing to receive more information about the study or not. If the participant is interested to receive more information about the study,  a phone call is made to provide further information and answer questions. Subsequently another text message is sent where participants are asked to answer if they are willing to participate or not. The reason for the varying patient approach is that the Norwegian Regional committees for medical and health research ethics does not authorize recruitment by telephone calls, as this may be perceived as undue pressure to participate. Eligible patients who are willing to participate are invited to the study center to sign written informed consent and to undergo baseline measurements. Patients who choose not to participate in the PREV-Ex study are asked, but not required, to provide a reason for non-participation. The study will be conducted in full conformance with the principles of the “Declaration of Helsinki.”

